**Discussion:**

This research attempts to verify the clinical efficacy and possible mechanism of HJD in the treatment of prediabetes, and prove the consistency of HJD Formula Granules with HJD Elixation. This study also aims to provide a treatment that is both effective and safe for prediabetic patients.

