However, research on the efficacy and clinical adverse reactions of HJD in prediabetic patients is still lacking. In addition, while the decoction is effective, the preparation process is tedious and time-consuming. Granules can be taken after mixed with warm boiled water, which can bring great convenience to patients, but there still lack persuasive evidence of efficacy consistency between the two dosage forms. For this reason, we designed this study protocol to evaluate the effectiveness and tolerability of HJD in the prevention and treatment of prediabetes. In addition, it is also aimed to verify the consistency between the Elixation of Huoxue-Jiangtang Decoction (HJD Elixation) and the Formula Granules of Huoxue-Jiangtang Decoction (HJD Formula Granules).

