### Participants

#### Sample size

Sample size is calculated by PASS 15.0 software, with the significance level of 0.05. A total of 189 cases (63 cases in each group) are required to detect inter-group differences in 2.6 mmol/L postprandial 2 h glucose, with a statistical power of 90%. The sample size calculation assumes a standard deviation of 2.0 mmol/L and a shedding rate of 20%.

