
#### Primary outcomes

The primary outcome is to verify the clinical efficacy and possible mechanism of HJD in the treatment of prediabetes, and to prove the consistency of HJD Formula Granules with HJD Elixation.

It specifically includes the change value of HBA1c, FBG, 2hPG prior to and following treatment.

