### Statistical analysis

Primary, secondary, exploratory end points and safety assessments will be analyzed when the last patient completes the follow-up or drops out of the study. Analyses of clinical data will be performed by the principal investigator including subjects’ demographic, clinical, and laboratory data.

Continuous variables are used to evaluate the number of cases, mean, standard deviation, median, minimum, and maximum for demographic data and other baseline eigenvalues. Frequency and composition ratio are calculated using count and grade data. Descriptive results invole inferential statistical results (*p*-values).

For the analyses of laboratory data and clinical efficacy of drugs, chi-square test or Fisher’s exact test are used for counting data, while ANOVA and T test are used for measurement data. The grade data is analyzed by Ridit and CMH. The ratio or percentage of counting data is expressed, and the measurement data is expressed as mean ± standard deviation. All statistical tests are conducted by two-sided tests, with *P* < 0.05 indicating statistical significance. Multiple imputation will be used for missing data.

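### Proving that the two HJD forms are consistent is a primary aim, but the stated tests and sample size address only differences and cannot support that conclusion

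*Protocol article*

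**What the plan says.** The Primary outcomes section of the protocol article combines two aims: efficacy of HJD in prediabetes, and "to prove the consistency of HJD Formula Granules with HJD Elixation". The variables named for both are "the change value of HBA1c, FBG, 2hPG prior to and following treatment". The consistency aim recurs in the Discussion part of the abstract ("prove the consistency of HJD Formula Granules with HJD Elixation") and in the Background, where "it is also aimed to verify the consistency between the Elixation of Huoxue-Jiangtang Decoction" introduces the comparison with the granules.

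The Statistical analysis section states that "ANOVA and T test are used for measurement data" and that "All statistical tests are conducted by two-sided tests", with significance at P<0.05. It assigns tests by type of data, does not name the Granules-versus-Elixation comparison, and makes no exception for it.

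The Sample size section works "with the significance level of 0.05" and 90% power. It says that 189 cases, 63 per group, "are required to detect inter-group differences in 2.6 mmol/L postprandial 2 h glucose", assuming an SD of 2.0 mmol/L and 20% dropout. It gives no basis for a consistency conclusion.

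**The concern.** A difference test takes equality as its null hypothesis. It can produce evidence against consistency but never evidence for it. The article therefore pairs a primary aim with a method that cannot deliver it, which goes beyond leaving detail to another document.

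Under the stated tests, only a non-significant result could be put forward in favour of consistency. That result becomes more likely as the sample shrinks or the measurements become noisier, so a poorly run trial would find the conclusion easier to reach than a well run one. At stake is a claim that the two dosage forms have the same efficacy, which could be used to support substituting one for the other.

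**Working it through.** **Inputs.** SD 2.0 mmol/L, 20% dropout, 63 per arm, two-sided 0.05, 90% power and a difference of 2.6 mmol/L in 2-hour glucose (2hPG), all from Sample size. Evaluable per arm: 63 × 0.8 = 50.4, taken as 50. That the SD applies to the change in 2hPG is an assumption. The article states no margin, so the margins below are assumptions shown as a range.

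**The plan's own figure.** n per arm = 2 × [SD × (1.960 + 1.282) / difference]². With 2.6 and 2.0 this is 12.4, so 13, and 13/0.8 gives 17 per arm, not 63. A difference of 1.3 with SD 2.0 gives 49.7, so 50, and 50/0.8 = 62.5, so 63. An SD of about 4.0 with 2.6 also returns 63. The failure to reproduce is a separate point. It matters here because 1.3 mmol/L is not a figure in the document; it enters below only as half of the stated 2.6.

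**Precision of Granules versus Elixation.** SE = 2.0 × √(2/50) = 0.40 mmol/L. With 98 degrees of freedom the 95% CI half-width is 1.984 × 0.40 = 0.79.

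**Probability that the difference test is non-significant** when the forms truly differ (noncentral t, noncentrality = difference/SE):

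| True difference (mmol/L) | Difference/SE | P(non-significant) |
|---|---|---|
| 0.65 | 1.625 | 64% |
| 0.8 | 2.0 | 49% |
| 1.0 | 2.5 | 30% |
| 1.3 | 3.25 | 10% |

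Noise moves this in the wrong direction. If the SD were 2.5, SE = 2.5 × 0.2 = 0.50, and a true difference of 1.0 would have ratio 2.0. The miss rate would then be 49% instead of 30%.

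**Power of an equivalence analysis** if the forms are identical, requiring the whole CI inside ±margin. In normal approximation, power = 2Φ(margin/SE − z) − 1, with z = 1.960 for the 95% CI and 1.645 for the 90% CI. At margin 1.3 with the 95% CI: 2Φ(3.25 − 1.96) − 1 = 2Φ(1.29) − 1 = 80%; using t, 79%. The t-based results are:

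| Margin (mmol/L) | 95% CI | 90% CI |
|---|---|---|
| 1.3 | 79% | 89% |
| 1.0 | 39% | 60% |
| 0.65 | about 0% | 3% |

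At 0.65 the expected 95% half-width (0.79) already exceeds the margin, so success is practically impossible even for identical products.

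**The case against.** Four points can be made for the protocol.

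First, nowhere does it say that P≥0.05 will be taken as consistency. A reader might infer that rule, but the article states no decision rule for this aim. The objection stands as far as it goes. What remains is that no test stated can support the conclusion.

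Second, a reader might infer that the trial would usually call the forms consistent even if one had lost half its benefit. The documents do not support this. The stated effect is 2.6 mmol/L, half of it is 1.3, and a shortfall of that size is missed only about 10% of the time. The 64% figure is for 0.65, which is half the benefit only if the true benefit is 1.3, a value the article does not give. For the same reason it cannot be said that this sample size is too small for a margin of half the effect: at 1.3 the equivalence power is 79% to 89%.

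Third, the full protocol or analysis plan may contain a margin and a CI rule, so their absence from the article is not in itself a fault. That is fair. But the article says that all tests are two-sided difference tests and bases the sample size on a difference alone. An equivalence analysis held elsewhere would not agree with that text.

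Fourth, the article's main Discussion section describes the goal as investigating the effectiveness and difference of the two forms, which difference tests do fit. This shows that the wording of the aim is unsettled. It does not remove the aim of proof from Primary outcomes or the abstract.

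**Conclusion.** The point holds as a mismatch between a stated primary aim and the stated method. Two-sided difference tests and a sample size based on a difference cannot prove consistency, whatever the true effect size. This conclusion rests on the text alone.

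The size of the problem depends on assumptions: 50 evaluable per arm, SD 2.0 mmol/L and 2hPG as the variable. On these, true differences of 0.65 to 1.0 mmol/L are missed 64% to 30% of the time, and 1.3 about 10%. Whether the planned size could support an equivalence conclusion depends wholly on the margin: it is workable near 1.3 mmol/L and inadequate at 1.0 or narrower. The correction should be made before unblinding, because a primary conclusion would otherwise have no analysis able to support it.

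**What to change.** 1. For Granules versus Elixation, replace the difference test by a confidence-interval (equivalence) analysis. Fix and justify a margin before unblinding, and conclude consistency only if the CI of the difference lies wholly inside it. Limit the sentence on two-sided tests accordingly.
2. Either name 2hPG as the variable that decides consistency, or set a margin for each of HbA1c, FBG and 2hPG and say how the three results combine.
3. State the confidence level and the power at the chosen margin.
4. If the justified margin is too narrow for this sample size, change the aim from proving consistency to estimating the difference with its 95% CI, wherever the aim appears.
5. In either case, state that P≥0.05 is not evidence of consistency.

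The cost is a change of wording in the protocol and analysis plan and one CI analysis; no new data or visits are needed. The downside is that the trial may have to make a weaker claim than proof if the interval is too wide.

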**Methods:**

This is a prospective, randomized, double-blind, and placebo-controlled clinical trial. A total of 183 participants are randomly assigned to HJD Formula Granules plus lifestyle intervention, HJD Elixation plus lifestyle intervention, and placebo plus lifestyle intervention. All subjects undergo 1 day of screening before participating in the study, followed by 84 days of drug intervention and observation. During and after treatment, the main outcome measures include fasting blood glucose and 2-hour postprandial blood glucose.

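### The abstract and body give different primary outcome lists, and each test is made at P < 0.05 with no rule on what counts as success; if any endpoint counts and the placebo comparisons are ungated, the false-positive risk is about 15–25%

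*Protocol article*

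**What the plan says.** Four places in the protocol article bear on this.

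- **Abstract, Methods:** "the main outcome measures include fasting blood glucose and 2-hour postprandial blood glucose". HbA1c is not named.
- **Primary outcomes:** "It specifically includes the change value of HBA1c, FBG, 2hPG prior to and following treatment". The same section sets two aims, efficacy of HJD and consistency of the two dosage forms. It does not rank the three measures or say whether one or all must succeed.
- **Sample size:** 63 per arm are "required to detect inter-group differences in 2.6 mmol/L postprandial 2 h glucose", "with the significance level of 0.05" and 90% power. No power basis is given for fasting glucose or HbA1c, and the 0.05 is not divided.
- **Statistical analysis:** "All statistical tests are conducted by two-sided tests", with significance at P < 0.05. Continuous data are analysed by ANOVA and t test. The text does not say whether the ANOVA must be significant before the t tests are read.

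Randomization is 1:1:1 to granules, elixation and placebo, so each endpoint offers two comparisons with placebo and one between the two HJD forms.

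**The concern.** The primary endpoint decides what the trial may claim, and here it can be read in two ways. HbA1c is primary in the body and absent from the abstract, so its status could be settled after the results are known.

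Three endpoints and two placebo comparisons give six efficacy tests, each at 0.05. As written, a form of HJD could be called effective on any one of its three endpoints. The 5% error rate that a reader attaches to a primary result would then not hold.

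This does not rest only on detail that an analysis plan might supply. The choice of primary endpoint belongs in the protocol, and the blanket 0.05 rule is stated text.

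**Working it through.** **The plan's own figure.** The sample size inputs are a 2-hour glucose difference of 2.6 mmol/L, SD 2.0, two-sided alpha 0.05, 90% power and 20% dropout.

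- n per arm = 2(1.960 + 1.282)² × 2.0² / 2.6² = 12.4, so 13.
- With dropout, 13 / 0.8 = 16.25, so 17 per arm and 51 in total.

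The stated 189 (63 per arm) does not follow from these inputs. With a difference of 1.3, n = 2(3.242)² × 4 / 1.69 = 49.7, so 50, and 50 / 0.8 = 62.5, so 63. That difference is not in the document. The mismatch is a separate matter, but it affects the cost of adjustment below.

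**Error rate, inputs.** The three endpoints come from Primary outcomes, the three equal arms from Randomization, and two-sided 0.05 per test from Statistical analysis. The correlation between endpoints is not in the document and is assumed to lie between 0 and 0.9.

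**Bound.** Six independent tests would give 1 − 0.95⁶ = 26.5%. The true figure is lower because both comparisons share the placebo arm and the endpoints are correlated.

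**Simulation under no effect.** 200,000 draws of three equal arms, any one significant test counting:

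| Reading | Correlation 0 | 0.5 | 0.9 |
|---|---|---|---|
| 3 endpoints, 2 placebo comparisons, ungated | 24.9% | 22.0% | 14.8% |
| Same, only findings favouring HJD | 13.1% | 11.1% | 7.4% |
| 3 endpoints, all 3 pairs, ANOVA gate per endpoint | 14.2% | 12.8% | 8.5% |
| Abstract's 2 endpoints, 2 placebo comparisons, ungated | 17.2% | 16.2% | 12.8% |

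**One endpoint only.** With a single primary endpoint, the two ungated placebo comparisons still give 9.0%. An ANOVA gate brings one endpoint to 5.0%. Naming one endpoint is therefore not enough without a gate, a sequence or an alpha split.

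**Cost of control.** Take 50 evaluable per arm, since 63 × 0.8 = 50.4. The standard error of a difference is 2.0 × √(2/50) = 0.40.

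- At the stated difference, 2.6 / 0.40 = 6.5. Against the critical value 2.24 for alpha 0.025, power is above 99%.
- At an assumed difference of 1.3, 1.3 / 0.40 = 3.25. Noncentral-t power is 89.6% at alpha 0.05 and 83.3% at 0.025. Under Holm, 83% is a floor, because the second comparison is tested at 0.05 once the first succeeds.

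**The case against.** Several counter-arguments have force.

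- **The abstract's list may not be exhaustive.** It says that the measures include two outcomes. This softens the mismatch but does not remove it, since an abstract that names two of three primaries leaves the third uncertain.
- **Sizing on 2-hour glucose might be read as a third, conflicting definition of the primary.** It is not. A trial with several primaries may be sized on one. It shows only that the other two have no stated power basis.
- **ANOVA may be meant as a gate.** The text allows that reading, and it lowers the error to about 8.5–14%, still above 5%. The text does not require it.
- **All three endpoints may have to succeed.** There would then be no inflation across endpoints. The document does not say this either.
- **A reader might count nine pairwise tests, with an error of about 19–32%, as chances of a false success.** That family is wrong for efficacy. The stated aim for granules versus elixation is consistency, so a significant difference there would count against the aim.
- **Two-sided tests also produce false findings that favour placebo.** True, and counting only those in favour of HJD gives about 7–13%.
- **Hierarchy and order of testing are often left to an analysis plan.** This stands as far as it goes. It does not cover the differing lists, or a stated rule that puts every test at 0.05.

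**Conclusion.** The point holds with its conditions attached. The primary list differs between abstract and body, only 2-hour glucose is sized, and P < 0.05 applies to every test with no multiplicity control and no any-or-all rule.

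The chance of at least one false-positive primary test against placebo is about 15–25% if any of the three endpoints counts and the comparisons are ungated. The range reflects assumed endpoint correlations of 0.9 to 0. On the other any-endpoint readings tabulated it is lower but still above 5%.

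A reader might infer a flat false-claim rate of 20–30%. The documents do not support that without conditions, because they fix neither the success rule, nor the gating, nor the correlation. The firm part of the finding is that they leave this choice open until after the data are seen.

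**What to change.** Name change in 2-hour postprandial glucose from baseline to day 84 as the single primary endpoint, since it is the only one with a sample-size basis. Make fasting glucose and HbA1c key secondary endpoints, and give the same list in the abstract and the body.

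Control the two placebo comparisons by one prespecified method:

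- a fixed sequence, in which the second HJD form is tested at 0.05 only if the first succeeds at 0.05; or
- Holm, in which the smaller p-value is tested at 0.025 and the other at 0.05 if the first succeeds.

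State whether ANOVA has any gating role. Requiring all three endpoints to succeed would also remove the inflation across endpoints, but the two placebo comparisons would still need control. Date the change before unblinding, which the Blinding section places after data lock.

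The cost is a wording amendment. On the stated inputs, with 50 evaluable per arm, power stays above 99% after adjustment. Only if the planning difference were really 1.3 mmol/L (an assumption) would power for a placebo comparison fall, from about 90% to no lower than about 83% under Holm. A fixed sequence costs the first comparison nothing.

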#### Secondary outcomes

The secondary outcomes are to evaluate the comprehensive effect of HJD Formula Granules and HJD Elixation, specifically including:Oral LA threshold determination.Dietary preference assessment.Changes of body weight and BMI.Time of blood glucose reaching standard.Changes of fasting C-peptide and 2-hour postprandial C-peptide.Changes of cytokines such as CRP, PCT, IL-6 and Adiponectin.

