#### Inclusion criteria

Meet the diagnosis of “prediabetes”, namely, the criteria of “impaired fasting glucose” and “impaired glucose tolerance” in the classification of glucose metabolism state proposed by WHO in 1999 [28]. Which means that fasting glucose ≥6.1 mmol/L, < 7.0 mmol/L and/or OGTT 2-hour glucose ≥7.8 mmol/L, < 11.1 mmol/L.≥18 years old and < 70 years old.HBA1c ≤6.5%.Patients who have not participated in any interventional clinical study or clinical trial in the past 3 months.Patients who are able and willing to sign written informed consent and complete the study.

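### Time to reaching the glucose standard is censored at 84 days, but the only rules it falls under are ANOVA/t test and blanket imputation, which dilute a real effect and can reverse it if treatment adds late responders

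*Protocol article*

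**What the plan says.** Under Secondary outcomes, the Protocol article lists "Time of blood glucose reaching standard". The text shown does not define the standard, name the glucose measure or measures it uses, or say what happens to a participant who never reaches it. The abstract describes one day of screening "followed by 84 days of drug intervention and observation", so follow-up for this outcome ends at day 84. The Sample size section also allows for 20% dropout.

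The Statistical analysis section states that primary, secondary and exploratory end points will all be analysed. It then allots methods by type of data:

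- counts: "chi-square test or Fisher’s exact test are used for counting data"
- continuous values: "ANOVA and T test are used for measurement data"
- ordered categories: "The grade data is analyzed by Ridit and CMH"
- missing values: "Multiple imputation will be used for missing data"

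No survival or other censoring-aware method appears in the article. Entry requires raised fasting glucose "and/or OGTT 2-hour glucose ≥7.8 mmol/L" (Inclusion criteria), so a participant may already be normal on one of the two measures at baseline.

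**The concern.** A time to reaching a target is known only for those who reach it within the window. For the rest, the data say that the time exceeds the last assessment. That is censoring, not a missing value. The group may well be large: the Discussion cites a multi-centre trial of TCM granules in which glucose returned to normal in 41.8% of treated and 27.8% of control patients after 12 months. So 100 − 41.8 = 58.2% and 100 − 27.8 = 72.2% did not normalise in a period far longer than 84 days.

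If a time in days is treated as measurement data, two routes are open. One averages times among attainers only. That is not a randomised comparison, because treatment itself decides who enters the subset. The other treats non-attainers as missing and imputes a time for them from those who did attain. Neither uses the main evidence of benefit, which is that more people reached the standard.

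**Working it through.** The plan gives no event count, power or effect size for this outcome (its sample size concerns 2-hour glucose), so there is no figure to reproduce. The check asks what the written rules would do.

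**Inputs.** The 84-day horizon and 63 per arm come from the article. Assessments at days 28, 56 and 84 are an assumption, inferred from the 28-day drug supply (Intervention). The attainment rates are assumptions too.

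**Formulas.** Let p₁, p₂, p₃ be the probabilities of first reaching the standard at days 28, 56 and 84, with P = p₁ + p₂ + p₃.
- Mean among attainers = (28p₁ + 56p₂ + 84p₃) / P
- Restricted mean to day 84, counting everyone = 28p₁ + 56p₂ + 84p₃ + 84(1 − P)

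**1. Added late responders.**
- Active, 20% of those remaining at each visit: 0.200, 0.160, 0.128; P = 0.488. Attainers: (5.6 + 8.96 + 10.752) / 0.488 = 51.9 days. Everyone: 25.312 + 84 × 0.512 = 68.3 days.
- Placebo, 20%, 5%, 0% of those remaining: 0.200, 0.040, 0; P = 0.240. Attainers: (5.6 + 2.24) / 0.240 = 32.7 days. Everyone: 7.84 + 84 × 0.760 = 71.7 days.

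Active is faster by 71.7 − 68.3 = 3.4 days over everyone, yet looks 51.9 − 32.7 = 19.2 days slower among attainers.

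**2. Constant rates, 30% against 10% of those remaining per visit.**
- 30%: 0.300, 0.210, 0.147; P = 0.657. Attainers: 32.508 / 0.657 = 49.5 days. Everyone: 32.508 + 84 × 0.343 = 61.3 days.
- 10%: 0.100, 0.090, 0.081; P = 0.271. Attainers: 14.644 / 0.271 = 54.0 days. Everyone: 14.644 + 84 × 0.729 = 75.9 days.

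The direction is right, but a gap of 75.9 − 61.3 = 14.6 days shrinks to 54.0 − 49.5 = 4.5 days.

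**3. Simulation.** 63 per arm, 2,000 runs, no dropout, two-sided 0.05. Three analyses were compared: a t test among attainers; imputation of non-attainers' times within arm (normal model, 10 imputations) followed by a t test; and the log-rank test. 'Wrong' means significant in favour of control. Scenarios A and C borrow the cited 12-month rates as 84-day rates.

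| Scenario (control vs active attaining) | Attainers-only t test, wrong | Imputation + t test, wrong | Imputation + t test, right | Log-rank, right |
|---|---|---|---|---|
| A: 27.8% vs 41.8%, extra responders late | 23% | 21% | under 1% | 32% |
| B: 30% vs 60%, extra responders late | 78% | 77% | 0% | 87% |
| C: 27.8% vs 41.8%, proportional hazards | 1% | 2% | 4% | 40% |
| D: 30% vs 60%, proportional hazards | 1% | 1% | 7% | 94% |

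The log-rank test was never significant in the wrong direction. Scenario A splits attainment over the three visits as 14/8/5.8% in control and 14/13/14.8% in active, so active is never behind at any visit. Its attainer means are 47.7 days in control and 56.5 in active, against restricted means of 73.9 and 72.5. In Scenario C, in continuous time, the attainer means are 39.7 days in control and 38.2 in active: nearly equal despite a hazard ratio of 1.66.

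**The case against.** The strongest reply is that the article never links a test to this outcome by name. Its rules are generic, the article is condensed, and a fuller analysis plan may name a survival method. It would therefore go too far to say that the plan specifies a t test for this outcome, or that it orders imputation of times for people observed to day 84 without the event. Such people are arguably not missing at all. Both readings follow from broad rules, not from an explicit statement.

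The listed methods are also not all unusable. Visit of attainment with 'not reached' as the last category is ordered data that Ridit or CMH could handle, and chi-square could compare proportions at standard. The article does not say that it will use them this way.

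A reader might also infer that the written analysis would generally make an effective product look worse than placebo. The documents do not support that. Reversal needs the added responders to be late, under rates and visit days the article does not give. Under constant or proportional rates the direction holds on average.

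Finally, being normal on one measure at entry is a problem only if the standard is scored on that measure alone.

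What stands is that the section covers secondary end points, states a rule by data type that places a time in days under ANOVA or t test, and states an imputation rule without exception. That is a stated rule which does not suit an outcome the article itself names, not merely detail left for later.

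**Conclusion.** The concern holds in a limited form. The outcome is right-censored at 84 days and by dropout, and the rules as written lead to an attainers-only comparison or to imputed times. The dependable consequence is dilution and lost power: under proportional hazards with 30% against 60% attaining, imputation plus t test finds the benefit in 7% of simulated trials and log-rank in 94%. Reversal is possible but conditional on late added responders, as in 51.9 against 32.7 days among attainers while 49% against 24% normalise.

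These sizes rest on assumed visits at days 28, 56 and 84, on assumed attainment patterns, on 12-month rates borrowed for 84 days in two scenarios, and on one particular imputation model. They show what the rules can do; they do not forecast this trial. The outcome is secondary, so the primary conclusion is unaffected, but the change should be made before unblinding.

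**What to change.** 1. State that this outcome is excluded from the ANOVA/t test rule and from the imputation rule; no times are to be imputed for participants who did not reach the standard.
2. Define the standard so that no participant meets it at entry. For example, require both fasting and 2-hour glucose to be below the lower limits in the Inclusion criteria (6.1 and 7.8 mmol/L). Every participant has at least one value at or above its limit at entry.
3. Analyse all randomised participants as time to the first scheduled assessment at which the standard is met, censored at the last glucose assessment. Use Kaplan-Meier curves and a log-rank or discrete-time (complementary log-log) comparison.
4. Report the proportion at standard by day 84 alongside.
5. Check the visit schedule first, since the text shown does not confirm that both measures are taken at interim visits. If they are not, base the definition on the measures available, still ensuring that nobody meets it at entry, or compare the proportion at standard at day 84 by chi-square instead.

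The cost is a few sentences in the analysis plan. With the fallback in step 5, no new data are needed.
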